### Power calculation

We based our power calculation on the primary outcome to detect at least a 35% difference in mosquito count between the intervention and control arm at a significance level (p-value) of 5%. We explored within-class correlation and the statistical distribution of our primary outcome using data on adult mosquitoes collected in 2022 by ASPB using data from artificial intelligence (AI)-driven smart traps [27]. Our analysis showed independence between weekly measurements, and the data followed a Negative Binomial distribution. Therefore, we performed the power calculation in *R* [28] using the *power_NegativeBinomial* function of the PASSED package ([28,29]). Assuming a minimum detectable difference in mosquito counts of 35% between the intervention and control arms and a significance level of 5%, we estimate a statistical power of at least 90% value for our sample of 44 drains. Further details of the power calculation are given in S1 File (Section: power calculation).

### Assignment of the intervention

#### Sequence generation

From the pool of 158 eligible drains, we allocated 44 drains 1:1 to the intervention or control arm, respectively, using a simple randomisation algorithm we developed in *R* [28]. The remaining drains within 200 m of a trial drain were eliminated from the eligibility pool. The process was repeated, alternating assignments between intervention and control arms until no drains remained for selection. We present details in S1 file (Section: Allocation of intervention and concealment mechanism).

#### Implementation

We wrote an *R* script for the selection of drains. The intervention allocation arm (i.e., intervention or control arm) was randomly assigned the letter code A or B, and two sets of shapefiles for the locations of selected drains were generated. The first showed both the intervention arm and letter code assignment for ASPB and BCASA, which are responsible for implementing the storm drain modification and collecting entomological data; the second included only the letter code which we shared with the blinded biostatisticians conducting the analysis. ASPB and BCASA used the allocation results and inspected the drains assigned to the intervention arm for the feasibility of the modification. If the modification was not possible, we assigned the next eligible drain.

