### Outcomes

Our objective in this trial is to assess the impact of storm drain modifications on *Ae. albopictus* and *Cx. pipiens* mosquito numbers inside intervention and control drains. Our primary outcome is the combined total counts of adult *Ae. albopictus* and Cx. *pipiens* mosquitoes sampled at each drain. The secondary outcome is drain activity defined as the presence of either adult mosquitoes or *Ae. albopictus* and *Cx. pipiens* larvae (L1-L2, L3-L4, and pupae stages) in drain water inside the drains. We sample water elements to collect adult mosquitoes and larvae at these alternative breeding sites. We also measured the depth of water (cm) in corresponding drains. One trained ASPB technician measures the primary and secondary outcomes starting on 26 June 2023 and continuing until no mosquitos are detected, visiting each participating drain once per week.

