### Adult mosquito collection

Our ASPB field technician uses an entomological aspirator (Improved Prokopack Aspirator Model 1419 from John W. Hock Co., powered by a 12 v 9.0 Ah valve-regulated, rechargeable sealed lead battery) to collect adult mosquitoes at specified drains. Wearing gloves, the technician assembles the aspirator consisting of the vacuum and the sample collection vesicle on-site. Holding the aspirator at a minimum one-meter horizontal distance from the drain, the technician approaches the drain and prepares for mosquito capture. The technician stomps on the drain to disturb resting mosquitoes and prompts them to take flight while simultaneously using the aspirator to capture escaping mosquitoes or those resting nearby. The technician subsequently opens the storm drain and systematically vacuums the interior space and walls to capture any resting mosquitoes. If water is present in the drain, the technician vacuums the walls closest to the water at arm's length, as mosquitoes tend to rest in these areas. If there is no water, the technician vacuums at arm's length to cover the entire interior space.

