### Laboratory evaluation and storage of biological specimens

Following collection, we transfer the samples to the ASPB laboratory, where they will be stored at −20 °C. We morphologically identify samples using a stereoscope to classify them by species (in the case of *Culex*, to species complex) and sex. We store mosquito samples (by assigning a unique identifying number) for at least two years following the completion of the trial.

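### Arm labels go to the agencies that collect the mosquitoes and only the analysts are blinded, while the primary count rests on hand aspiration with a wet/dry routine and on laboratory reading with no stated masking

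*Protocol article*

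**What the plan says.** The Implementation section of the protocol article describes two sets of location files. Of the one that carries the arms it says: "The first showed both the intervention arm and letter code assignment for ASPB and BCASA, which are responsible for implementing the storm drain modification and" also, as the sentence goes on, for gathering the mosquito data. The other file is for the analysts: "the second included only the letter code which we shared with the blinded biostatisticians conducting the analysis". The agencies also act on the labels: "ASPB and BCASA used the allocation results and inspected the drains assigned to the intervention arm" to see whether the modification was feasible. Nobody other than the biostatisticians is described as blinded.

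The Outcomes section names the assessor: "One trained ASPB technician measures the primary and secondary outcomes", with one visit per drain per week. Under Adult mosquito collection, the technician stomps on the drain, catches what escapes, then opens it and "systematically vacuums the interior space and walls to capture any resting mosquitoes". Two instructions follow. If water is present, the walls nearest the water are vacuumed. If the drain is dry, the aspiration is to cover the whole interior.

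Under Laboratory evaluation, specimens go to ASPB's own laboratory: "We morphologically identify samples using a stereoscope to classify them by species" and sex. A unique number is mentioned in connection with storage. The section says nothing about masking. The Limitations section does not mention unblinded outcome assessment.

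**The concern.** Blinding is given to those who make no measurement and is not described for the agency that makes all of them. That agency also introduced the modification, and the stated hypothesis is directional. The catch is manual, so the number recorded depends on how long and how thoroughly the technician searches. With a single assessor, an expectation effect would not average out across observers.

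A second route needs no expectation at all. The Interventions section says that the modification is meant to remove standing water, and the aspiration instruction changes with standing water. A neutral technician who follows the text could therefore search modified and unmodified drains differently.

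Either way, a difference in capture between arms is inseparable from the treatment effect. The drain random effects, the GEE check, the weather and land-cover adjustments and the blinded analysts all come in after the count has been made. The results are meant to guide a city-wide expansion, so a shift in the primary rate ratio matters.

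**Working it through.** **Who knows what, and when**

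- Arm labels: ASPB and the water authority, BCASA (Implementation).
- Letter code only: the biostatisticians (Implementation).
- Field catch: one ASPB technician at every drain (Outcomes; Assessment and collection of outcomes).
- Identification and sexing: the ASPB laboratory (Laboratory evaluation). The article does not say whether the unique number hides the drain or the arm.

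Every step from catch to count thus lies with an agency that holds the arm labels, and the only stated masking starts once the count exists.

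**Coverage.** The general instruction is to vacuum the interior and walls. The wet and dry instructions that follow differ in target: walls nearest the water, or the entire interior. The text does not settle whether a wet drain also gets the full interior. If it does not, the arm with more dry drains is searched more widely.

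**How far a capture difference moves the estimate.** Let c be the chance that a mosquito present is caught and counted in an intervention drain, divided by that chance in a control drain. The expected observed rate ratio is the true ratio times c. The target is a 35% difference (Power calculation), a ratio of 0.65. The share of the target that c alone produces is ln c / ln 0.65. The document gives no detection figure, so every value of c is an assumption.

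- c = 0.90: −0.1054 / −0.4308 = 0.245, about 24% of the target. With no true effect the expected ratio is 0.90. With a true 0.65 it is 0.65 × 0.90 = 0.585.
- c = 0.80: −0.2231 / −0.4308 = 0.518, about 52% of the target. With no true effect the expected ratio is 0.80. With a true 0.65 it is 0.65 × 0.80 = 0.52.

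**What that does to the test.** The plan's own figure, at least 90% power with 44 drains at 5%, cannot be reproduced from the article: the control mean, the dispersion and the number of weekly counts are not given there, and it refers to S1 File for details. The point does not dispute that figure. Taking it as exactly 90% and two-sided (sidedness is not stated), the implied standard error of the log rate ratio is 0.4308 / (1.960 + 1.282) = 0.133.

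With no true effect, the chance of a significant result favouring the intervention is Φ(−1.960 − ln c / 0.133):

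| c | chance |
|---|---|
| 1.00 | 2.5% |
| 0.95 | 5.8% |
| 0.90 | 12.2% |
| 0.85 | 23.1% |
| 0.80 | 38.9% |

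If the power is above 90%, the standard error is smaller and these chances are larger.

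**The opposite direction.** If dry drains are searched more fully, c exceeds 1. With a true ratio of 0.65 and c = 1.10, the expected ratio is 0.65 × 1.10 = 0.715. Power becomes Φ((0.4308 − 0.0953) / 0.133 − 1.960) = Φ(0.56), about 71% instead of 90%.

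**The case against.** Several stronger readings are tempting, and the documents do not support them.

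- A reader might infer that the laboratory staff know the allocation. The article shows this only at agency level: the file goes to ASPB, and the laboratory belongs to ASPB. Nothing says that the people at the stereoscope see the file. S1 File has a section on allocation and concealment that is not shown and may add masking steps. It would not change who, on the article's own account, received the arm labels.
- A reader might infer that withholding the file would blind the technician, or that the stomping phase could be masked because it precedes opening. Every drain is opened at each weekly visit, and the modification is visible inside. Withholding the file protects at most the first visit, so field blinding is largely unattainable.
- A reader might infer that any bias must favour the intervention. Expectation would push that way, but fuller vacuuming of dry drains could push the other way.
- A reader might infer that laboratory error feeds straight into the primary outcome. Confusing the two target species leaves their combined count unchanged. Only miscounting, or assignment to or from another species, would alter it. Masked reading matters more for the species and sex strata. The approximate larval numbers are neither a primary nor a secondary outcome.

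The article also refers to an established sampling protocol that may already fix the aspiration time, and using one trained technician removes differences between observers. Both points are fair. Neither removes the water-dependent instruction printed in the article, and a single observer does not protect against an expectation held by that observer.

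**Conclusion.** The point holds as a partly avoidable exposure to assessment bias in the primary outcome, and it arises from choices that the article states. The arm-labelled file goes to the collecting agencies, blinding is described for the analysts alone, laboratory masking is not stated, and the aspiration instruction varies with the condition that the intervention alters.

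Whether bias will occur, how large it would be and which way it would run cannot be determined from the documents. The 24% and 52% of the target effect, and the rise from 2.5% to about 12% or 39% in false positive results favouring the intervention, rest on assumed capture ratios of 0.90 and 0.80. The percentages for the test also assume exactly 90% two-sided power. They show that modest differences in capture would matter at the trial's planned precision. They do not show that such differences exist. The design is not invalidated, and the sample size, randomisation and model need no change on this account.

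**What to change.** - Limit the arm-labelled file to the ASPB and BCASA staff who need it to carry out the modification.
- Label vials with a code that carries neither drain ID nor arm. Have the existing laboratory identify, sex and count without access to the key. Specimens are to be kept for at least two years after the trial, so those already read can be re-read masked as a check.
- Use one aspiration procedure at every drain, with the same fixed time and the same coverage whether or not water is present. If the sampling protocol already fixes this, say so and bring the wet and dry wording into line with it. If visits have already been made under the water-dependent routine, report that.
- State in the Limitations section that field collection is unblinded, because the modification is visible once a drain is opened.

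The cost is a linkage key to maintain, relabelled vials and a timer. No extra staff are needed.

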### Criteria for excluding or modifying allocated interventions

Upon inspection, our partners at ASPB and the water infrastructure authority excluded drains that did not fit the inclusion criteria. We applied three exclusion criteria for selecting storm drains in our trial: (i) previously modified drains that were unreported in the public record, (ii) inaccessible drains in construction areas or where obstructed by public infrastructure, and (iii) obstruction from cars parked on top of the drains.

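### Feasibility inspection and replacement after allocation are described for the intervention arm only, so only that arm is conditioned on being modifiable, and the article does not settle whether controls had the same screen

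*Protocol article*

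**What the plan says.** All references are to the protocol article.

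- **Sequence generation.** From a pool of 158 eligible drains, 44 were allocated 1:1. Drains within 200 m of a selected drain were removed, and the process was repeated, "alternating assignments between intervention and control arms until no drains remained for selection".
- **Implementation.** Two location files were made. "The first showed both the intervention arm and letter code assignment for ASPB and BCASA"; the other carried only the letter code and went to the blinded analysts. The two agencies then used the allocation and "inspected the drains assigned to the intervention arm for the feasibility of the modification". The replacement rule follows directly: "If the modification was not possible, we assigned the next eligible drain". Nothing comparable is stated for drains assigned to control.
- **Criteria for excluding or modifying allocated interventions.** On inspection, the public health agency and the water authority "excluded drains that did not fit the inclusion criteria". The scope is given as "We applied three exclusion criteria for selecting storm drains in our trial". The list covers "previously modified drains that were unreported in the public record", "inaccessible drains in construction areas or where obstructed by public infrastructure", and drains blocked by parked cars. No arm is named.
- **Interventions.** The 22 control drains were left unmodified by the trial and are described as breeding sites.

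**The concern.** The trial is presented in Background and Objectives as the experiment that removes the confounding of an earlier observational study. That claim depends on the arms differing only by chance and by the modification.

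The order of events in Implementation works against this. Drains were allocated, the agencies were told the arm, and drains in one arm were then tested against a condition (can it be modified?) and swapped out if they failed. The intervention arm therefore contains only modifiable drains. The control arm, as described, contains whatever was drawn.

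Drains that cannot be modified may differ in structure, water retention or surroundings, and so in mosquito counts, whatever the intervention does. A control drain that had already been modified without record would act as a treated unit in the control arm. With 22 drains per arm, a few such drains matter. The land-cover and weather adjustments in Statistical methods are not aimed at modifiability and need not remove the difference.

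**Working it through.** **1. The two sections side by side.**

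| | Implementation | Criteria for excluding or modifying allocated interventions |
|---|---|---|
| Timing | After allocation | On inspection; timing relative to allocation not stated |
| Who | The two agencies, arm known | The same two agencies |
| Which drains | Intervention arm | No arm named |
| Test | Modification feasible | Previously modified, inaccessible, obstructed by cars |
| Consequence | Replaced by the next eligible drain | Excluded |

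If the exclusion section describes the same inspection as Implementation, controls had no screen. If it describes a trial-wide screen, controls passed the three listed criteria but still not the feasibility test, which has no stated control counterpart. On either reading the arms passed different filters. They differ only in how far apart the filters are.

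**2. The plan's own figure.** Power calculation states at least 90% power for 44 drains, a 35% difference (rate ratio 0.65) and a 5% level. The article gives no mean count, dispersion or number of weeks, so this can be neither reproduced nor refuted. With 22 per arm and a two-sided test, 90% power requires a standard error of the log rate ratio of

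|ln 0.65| / (1.960 + 1.282) = 0.4308 / 3.2415 = 0.1329.

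This standard error is used below only as a reference point.

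**3. Selection on feasibility, no true effect.** Let q be the share of drains that cannot be modified and r their mean count relative to the others. If they are replaced in the intervention arm only,

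expected rate ratio = 1 / [(1 − q) + q·r].

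| q | r = 0.5 | r = 1.5 | r = 2 |
|---|---|---|---|
| 0.10 | 1.053 | 0.952 | 0.909 |
| 0.20 | 1.111 | 0.909 | 0.833 |
| 0.30 | 1.176 | 0.870 | 0.769 |

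The same mechanism can produce an apparent benefit or an apparent harm. Values of q and r are assumptions; the article gives neither.

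**4. Dilution, if some controls were already modified.** Let f be the share of controls already modified, with a true rate ratio of 0.65 and power of exactly 90% at that value:

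observed rate ratio = 0.65 / (1 − f + 0.65f); power = Φ(|ln observed| / 0.1329 − 1.960).

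| Already modified, of 22 | f | Observed rate ratio | Power |
|---|---|---|---|
| 0 | 0 | 0.650 | 90% |
| 1 | 0.045 | 0.661 | 88% |
| 2 | 0.091 | 0.671 | 85% |
| 4 | 0.182 | 0.694 | 78% |

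The counts of modified controls are also assumptions.

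**The case against.** A reader might infer that only intervention drains were ever inspected, and that already modified or inaccessible controls remain in the trial. The article does not support that.

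- The three exclusions are stated for drains in the trial as a whole, and Interventions describes the controls as unmodified breeding sites.
- Eligibility criteria required mosquito activity in 2022 or standing water in early 2023. The modification is meant to remove standing water, so a previously modified drain should rarely qualify. The existence of the exclusion for unrecorded modifications shows that it could happen.
- Adult mosquito collection has the technician open and vacuum the drain, so a permanently inaccessible control could not be sampled.

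A reader might also see a contradiction between a pool run until exhausted and a later next eligible drain. That is weak: dropping a drain can release neighbours that had been removed only because they lay within 200 m of it. Allocation detail is also referred to S1 File, which is not shown.

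Finally, the dilution figures rest on assumed shares and on power of exactly 90%, where the article says at least 90%. Dilution also pulls towards no effect, so it does not threaten a positive result.

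All of this stands against the stronger reading. None of it supplies a control counterpart to the feasibility test and replacement in Implementation, which is a stated rule and not merely an omitted detail.

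**Conclusion.** The concern holds in a limited form. Implementation fixes a replacement step that comes after allocation, is carried out by agencies that know the arm, and is described for intervention drains only. As written, it conditions one arm on modifiability and not the other. The exclusion section leaves unclear whether controls had any equivalent screen. Non-modifiable or previously modified controls may therefore remain; the article does not show that they do.

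Size and direction are unknown. Under the assumed shares and count ratios, selection alone moves a null rate ratio to somewhere between 0.77 and 1.18. One to four already modified controls would move 0.65 to between 0.661 and 0.694. If no drain was replaced, or if controls passed the same screen including feasibility before outcome collection, most of the concern falls away.

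**What to change.** 1. Reconcile the two sections: state whether, when and by whom control drains were inspected, and against which criteria.
2. Apply one checklist, the three listed exclusions plus feasibility of modification, to the 22 control drains, using an assessor without access to outcome data.
3. Report an analysis restricted to drains passing the same screen in both arms, alongside the analysis of all 44 drains.
4. Report replacements by arm, reason and source, including whether each was drawn in random order and met the 200 m rule.
5. Analyse drains as originally allocated only where outcome data were collected on replaced drains. The article describes weekly visits to participating drains, so such data may not exist.

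The cost is a checklist at 22 drains already visited weekly, one added analysis and a short table. A few control drains may drop out of the restricted analysis; keeping the 44-drain analysis beside it makes the effect of that visible.

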## Data collection

### Assessment and collection of outcomes

We have scheduled an ASPB field technician to visit participating drains weekly between 7am and 12pm starting on 26 June 2023 and continuing until no mosquitos are detected. During each visit, our technician will collect data on the primary and secondary outcomes and the presence and depth of water in the storm drains. We have established a sampling protocol that our technician will follow, which includes the use of protective gear, including gloves and sturdy shoes. The equipment for the sample collection will remain distal from the drainage element (Fig. 4).

